### Data analysis

*Quantitative analysis*

Data will undergo de-identification prior to analysis. Baseline characteristics of participants will be presented, utilizing mean and standard deviation for continuous variables and frequency and percentage for categorical variables. The trial outcome analysis will adhere to the intent-to-treat principle. Generalized estimating equations (GEE) with a binomial distribution and log link function will be used for the primary binary outcome, with clustering specified at the PSU level, to assess the main and interaction effects of the four implementation techniques on adherence to BISC practices among primary healthcare clinicians. The model will account for robust predictors of outcomes, including baseline adherence scores and sociodemographic factors of clinicians^24-26^. Effect coding will be applied to each experimental condition, and subgroup analyses based on age, gender, clinician level, and facility will be conducted to further explore the impact of different technique combinations on BISC implementation. Sensitivity analyses, involving imputation of missing values through random forest, will be performed to validate the robustness of the findings^27^. For continuous outcomes, GEE models with a Gaussian distribution and identity link function will be employed, adjusting for the same covariates and clustering at the PSU level. In the analysis, control for covariates including clinician-related information (gender, age, professional title, and department) and patient-related information (gender, age, primary diagnosis, and smoking status). We will perform subgroup analyses on patient smoking status, level of tobacco dependence, and clinician department to investigate differences in BISC implementation among different types of clinicians for various types of patients.

Hypothesis tests will be two-sided, with statistical significance set at p<0.05. All statistical analyses will be performed using Stata version 16.0 and R version 4.5.2.

*Qualitative analysis*

Qualitative data analysis from stakeholders will be de-identified and imported into Nvivo 11.0 for transcription, organization, coding, and content analysis. Our qualitative data analysis will use a mixed approach, combining both deductive and inductive methods, to identify established themes, patterns, and new discoveries^28,29^. For the first phase of the study, data from our scoping review^30^ and stakeholder consultations were analyzed deductively using the Consolidated Framework for Implementation Research (CFIR)^31^ to identify barriers and facilitators. For the second phase, data from semi-structured interviews will be analyzed inductively to find new themes. These data will also be analyzed using NPT to evaluate how the BISC intervention is integrated and sustained in practice. To ensure our coding is reliable, two team members will independently code each interview, and any differences will be resolved through discussion.

The systematic decision-making process^32^, guided by data from the factorial trial, will be integral to this procedure. We will leverage the estimated main effects to identify techniques that have a statistically significant positive impact. We will also examine interaction effects to glean insights into potential synergies or antagonisms between the techniques. The final optimization of implementation strategies will be achieved by integrating information from both main and interaction effects, along with a consideration of the predetermined constraints of the optimization objective. This approach ensures that the final selection of techniques is the most effective and efficient combination.

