### Recruitment and informed consent

*Study setting*

The study will be conducted in primary healthcare institutions located in Guangdong Province, China, from January 2026 to December 2026. To ensure the generalizability of our findings across the diverse socioeconomic landscape of the country, we will strategically select institutions from three cities that represent a spectrum of economic development: a highly-developed city from the Pearl River Delta region, a moderately-developed city from either Eastern or Western Guangdong, and a less-developed city from Northern Guangdong. This deliberate selection allows us to rigorously test our implementation strategies under a wide range of conditions, from highly-resourced urban settings to more resource-constrained rural areas.

The selected institutions will include a variety of primary care settings, specifically community health service centers and township health centers/village health stations, to ensure a broad representation of primary care delivery models. We will recruit a sufficient number of institutions to meet the sample size requirements determined in the section sample size and power.

The institutional inclusion criteria are as follows: 1) the institution must have been a member of a compact medical consortium within the last three years; and 2) the institution must provide comprehensive primary healthcare services. The exclusion criteria for institutions include: 1) ongoing participation in any other smoking cessation intervention studies; and 2) ongoing participation in other implementation studies that are testing any of the specific implementation techniques used in our trial.

*Study population*

The study population is clinicians, encompassing licensed clinicians, licensed assistant clinicians, and certified village clinicians. Clinicians will be included based on the following criteria: 1) they have worked in a clinical capacity for at least six months; and 2) they provide outpatient and primary healthcare services. Conversely, clinicians will be excluded if they meet any of the following criteria: 1) they have previously received smoking cessation-related training or participated in a similar trial; 2) they are absent from work for one month or more; 3) they are a non-formal employee such as a temporary worker or rotational staff; and 4) they are currently participating in other studies related to any of the specific implementation techniques being tested in the present trial.

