*Sampling procedure*

This study will use a multistage, clustered sample design. The primary sampling unit (PSU), which is a regrouped unit of clinics or facilities, will serve as the randomization unit. The sampling process will be conducted in multiple stages (Figure 2). The first stage involves the purposive selection of three cities within Guangdong province to ensure a comprehensive representation of different socioeconomic development levels. Specifically, we will select one highly-developed city from the Pearl River Delta region, one moderately-developed city from either Eastern or Western Guangdong, and one less-developed city from Northern Guangdong.

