**Figure 2 F0002:**
[figure not shown]
Sampling procedure of primary healthcare facilities with 640 clinicians, Guangdong Province, China, January 2026 – December 2026

In the second stage, all primary healthcare institutions under the jurisdiction of the recruited local health authorities in these three cities will be included in the sampling frame. These institutions will then be regrouped into PSUs based on the number of clinicians. This ensures that each unit has a sufficient number of clinicians, preventing the exclusion of smaller institutions from the sampling process. The PSUs will then be sampled using a probability proportional to size (PPS) sampling method.

The study will be conducted as a cluster-randomized trial. The intervention will be delivered to the entire cluster (PSU), but the intervention’s effect will be measured at the clinician level. The measurement is based on the average performance of a random sample of clinicians within the cluster. This is achieved through unannounced standardized patient (USP) visits, which function as the final step of the sampling process. A minimum of 80 USP visits will be assigned to each experimental condition.

*Sample size and power*

Power analyses were conducted to determine the sample size needed to test the effect of the implementation strategies on our primary outcome, ‘clinician advice to quit’. The detailed definition and measurement of this outcome are provided in the section on study outcomes. Based on prior research, the baseline rate for this outcome was 33.9%^13^. Through stakeholder consultation, it was determined that a 40% increase in delivery, resulting in a final primary outcome of 47.46%, would be considered a clinically meaningful effect. Assuming a two-tailed test with an alpha level of 0.05 and a desired power of 0.8, a sample size of 28 participants per cluster is required. Accounting for the cluster-randomized design with a design effect (Deff) of 2 and adjusting for an anticipated 20% loss to follow-up, the sample size has been intentionally increased to further enhance statistical power for detecting higher-order interactions. Consequently, the required sample size for one experimental condition is approximately 80 participants. Given our study design with eight conditions (one condition per PSU, for a total of eight PSUs), this translates to 640 participants in total.

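### The planned subgroup analysis by facility has no technique comparison within any one facility, and the way PSUs are formed does not ensure one within each facility type

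*Protocol article*

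**What the plan says.** Under Data analysis (Quantitative analysis), the article plans that "subgroup analyses based on age, gender, clinician level, and facility will be conducted to further explore the impact of different technique combinations". *Facility* is not defined there. Two readings are open: the single institution, or a class of institution. For the second, Study setting names the classes, "specifically community health service centers and township health centers/village health stations", and Table 2 records institution location and level.

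The layout is fixed elsewhere:

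- Sampling procedure: "The primary sampling unit (PSU), which is a regrouped unit of clinics or facilities, will serve as the randomization unit".
- Sampling procedure, on how these units are made: "These institutions will then be regrouped into PSUs based on the number of clinicians". Facility type is not named as a criterion.
- Sampling procedure also states that the whole PSU receives the assigned intervention.
- Sample size and power: "one condition per PSU, for a total of eight PSUs".

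Study setting says of the choice of three cities: "This deliberate selection allows us to rigorously test our implementation strategies under a wide range of conditions".

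**The concern.** A subgroup analysis of technique combinations needs several combinations inside each subgroup. Age, gender and clinician grade can vary among clinicians in the same PSU, so each of those subgroups can span all eight conditions. Facility is different, because it is nested in the unit that was randomized. On the single-institution reading the listed analysis is empty. On the type reading it may hold only some of the conditions.

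If the analysis is run regardless, one facility's result under one combination is set against another facility's result under a different combination. Differences in baseline practice, resources and area could then be taken as evidence that a combination works in a given kind of facility.

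**Working it through.** **Inputs.** Eight conditions from a 2×2×2 design (Study design); eight PSUs with one condition each and about 80 clinicians per condition (Sample size and power); facilities nested in PSUs (Sampling procedure). That no institution is split across PSUs is inferred from the description of a PSU as a regrouped unit of facilities; the article does not say so outright.

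**Stated layout.** 8 × 80 = 640, which agrees with the article's total.

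**Reading 1: facility is a single institution.** Every clinician in an institution has the same values of the three effect-coded factors. The factorial design matrix inside an institution therefore has rank 1 (the intercept), and the number of estimable technique contrasts is 0. Equivalently, adding the eight factorial columns to a set of facility indicators adds no rank. With 1, 2 or 5 facilities per PSU (illustrative numbers), the rank is 8, 16 or 40 both before and after.

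**Reading 2: facility is a type or level.** The result depends on the make-up of the PSUs, which the article does not give.

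*(a) Every PSU holds both types.* Each type subgroup contains all eight conditions, and the full factorial has rank 8 of 8. The comparison exists.

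*(b) Each PSU holds one type only (an assumption, not in the article).* A type with k PSUs then has k of the eight conditions. An intercept and three main effects need four independent rows, that is, four corners of the cube that do not lie in one plane.

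| PSUs of the type | Possible sets | Main effects estimable | Orthogonal main effects |
|---|---|---|---|
| 3 | 56 | 0 | 0 |
| 4 | 70 | 58 | 2 |
| 5 | 56 | 56 | 0 |

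- k = 3: three rows cannot give rank 4.
- k = 4: 12 of the 70 sets are coplanar. Six are faces of the cube, where one technique has a single level. The other six are diagonal rectangles, where both levels of every technique occur but two techniques are completely aliased. 70 − 12 = 58. These fits leave 4 − 4 = 0 residual PSU degrees of freedom. Only the 2 half-fractions give orthogonal main effects (2/70 = 3%), and there each main effect is aliased with a two-way interaction.
- k = 5: no five corners are coplanar, so the main effects can always be fitted. With an odd number of PSUs no factor is balanced, so they are never orthogonal.

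Under (b), any split of the eight PSUs other than 4:4 leaves one type with three or fewer, so both types can be fitted only at 4:4.

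*(c) Some PSUs mixed, some not.* The result lies between (a) and (b).

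**Main analysis, for context.** The saturated factorial uses 8 of 8 PSU degrees of freedom, leaving 8 − 8 = 0. PSU differences are therefore already inseparable from the combinations in the trial as a whole.

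**The case against.** The strongest reply is that *facility* stands in a list of attributes that define classes, so type or level is the natural reading, and that an article may leave the definition of a subgroup to the fuller plan. Both points have weight. A reader might infer that no facility subgroup of any kind can contain the comparison. The article does not support that: under mixed PSUs each type contains all eight conditions, and PSUs of a single type are no better documented than mixed ones. The counts for three and four PSUs are therefore conditional illustrations, and the result for five PSUs is favourable.

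A reader might also take the Study setting sentence as a promise to test technique effects separately by setting. It concerns the selection of cities and generalizability, and the limitations section concedes that effectiveness may not carry over to other settings.

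Finally, the analysis is labelled exploratory, the optimization decision is described in terms of main and interaction effects without mention of subgroups, and confounding with the PSU affects every analysis in this trial. Subgroups by age or gender do not escape it.

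What the reply does not remove is the structural point. A later document can define the word, but it cannot create a contrast inside an institution, and it cannot ensure that a type occurs in every PSU when the PSUs are formed on clinician numbers.

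**Conclusion.** The point holds in a limited form. By single facility, the listed analysis has no technique contrast at all, given that institutions are not split across PSUs. By type or level, it has all eight conditions only if every PSU includes that type, and the sampling rule does not ensure this. Where it fails, facility differences are confounded with the combination in that subgroup, in addition to the confounding from having one PSU per condition. The size ranges from no loss (every PSU mixed) to main effects that cannot be estimated in a type (three or fewer single-type PSUs, or 12 of 70 sets of four). The article does not allow a choice within that range. The primary analysis is not changed by this point, and correcting the subgroup sentence does not cure the separate problem of one PSU per condition.

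**What to change.** In Data analysis:

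- Remove single facility as a subgroup variable and report facility-level rates descriptively.
- If facility type or level is to be kept, define it. Fit only exploratory technique-by-type terms for the main effects, from PSUs that contain both types.
- Make this conditional on those PSUs including both levels of each technique and being enough to estimate the three main effects. That means at least four PSUs with no two techniques aliased.
- If the condition is not met, report by type descriptively and make no claim that a combination works in a given type of facility.

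In Study setting, it is enough to avoid implying that technique effects are tested separately by setting.

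The cost is a change of wording. One exploratory subgroup may be lost. Restricting the terms to mixed PSUs can also remove whole conditions, because each condition has only one PSU; this is why the condition is needed.

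### Significance of the main effect is the only stated statistical criterion for identifying techniques, and the protocol's own inputs do not support the claim that this ensures the most effective combination

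*Protocol article*

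**What the plan says.** The stated primary objective (Introduction) is to identify the optimal set of implementation techniques. The decision step is at the end of the Data analysis section, under Qualitative analysis: "We will leverage the estimated main effects to identify techniques that have a statistically significant positive impact". Interactions are then examined for synergy or antagonism, and the final choice combines main effects, interactions and predetermined constraints. The paragraph closes: "This approach ensures that the final selection of techniques is the most effective and efficient combination". The test level is in the Quantitative analysis text: "Hypothesis tests will be two-sided, with statistical significance set at p<0.05".

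The section Sample size and power holds the only agreed effect size: "a 40% increase in delivery, resulting in a final primary outcome of 47.46%, would be considered a clinically meaningful effect". It plans 80% power, a design effect of 2 and 20% loss, arrives at about 80 clinicians per condition and 640 in total, and adds that "the sample size has been intentionally increased to further enhance statistical power for detecting higher-order interactions". The decision paragraph does not refer back to the agreed effect.

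**The concern.** In an optimization trial the main result is a set of in-or-out judgements on techniques. If significance is the statistical screen, two different findings can look alike: a technique shown to fall short of a worthwhile effect, and one whose interval covers both no effect and the full 40% increase. An effective technique lost in this way leaves the package recommended for scale-up, while the remainder is reported as the most effective combination.

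The closing guarantee could be defended only if the screen rarely missed a technique with the target effect. The sample-size section gives what is needed to check that.

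**Working it through.** **Inputs, all from Sample size and power.** Baseline 33.9%; target 47.46% (33.9% × 1.40, a difference of 13.56 points); two-sided alpha 0.05; power 0.80; design effect 2; 20% loss; 640 clinicians in eight PSUs, one per condition. Each main effect therefore compares 320 with 320 clinicians, in 4 against 4 PSUs.

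**The plan's own figure.** The text gives 28 per cluster as the number needed at these settings, before the design effect and loss.
- The two-proportion formula, n = [1.96√(2p̄(1−p̄)) + 0.842√(p₁(1−p₁)+p₂(1−p₂))]² / (p₂−p₁)², with p̄ = 0.4068, gives 205 per level of a technique, or 220 with continuity correction.
- A main effect needs both levels: 410 to 440 in total, or 410/8 to 440/8, about 52 to 55 per condition before the design effect.
- The figure 28 appears if only one level's n is spread over eight conditions: 220/8 = 27.5. Then 28 × 2 / 0.8 = 70, raised to about 80, and 8 × 80 = 640.
- For 80% power with design effect 2 and 20% loss, the total would be 410 × 2 / 0.8 = 1,025.

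**Power of the significance screen at 640.** The effective size per level is 320/2 = 160 without loss and 320 × 0.8/2 = 128 with 20% loss. With unpooled SE = √[(0.339×0.661 + 0.4746×0.5254)/m] and power = Φ(0.1356/SE − 1.96):
- m = 160: SE 0.0544, power 70.3%, miss 29.7%.
- m = 128: SE 0.0608, power 60.6%, miss 39.4%.

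Pooled variance gives misses of 30.4% and 40.1%. The log rate-ratio scale gives 31.8% and 41.4%.

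**How far this moves with the assumptions.**
- If effects multiply, as the planned log link implies, and one other technique also has a ratio of 1.4, the miss rate is 17% (no loss) to 26% (20% loss). If both others do, it is 5% to 11%.
- If effects add in points, other active techniques leave it at about 32% to 42%.
- A t reference with 4 to 6 degrees of freedom, reflecting 4 against 4 PSUs, raises it to about 45% to 60%.

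**Judging intervals against 1.40 instead.** On the log scale ln 1.40 = 0.3365.
- Full effect: SE = √[(0.661/0.339 + 0.5254/0.4746)/m] = 0.138 (m = 160) or 0.155 (m = 128). The upper bound falls below 1.40 in 2.5% of trials. The interval covers both 1 and 1.40 in 31.8 − 2.5 = 29% or 41.4 − 2.5 = 39%.
- Null technique at 33.9%: SE = √[2 × (0.661/0.339)/m] = 0.156 or 0.175. The upper bound falls below 1.40 in 58% or 49%, the lower bound exceeds 1 in 2.5%, and the remaining 40% or 49% are undetermined.
- The 95% interval for a full-effect technique spans 3.92 × SE = 0.54 or 0.61 on the log scale. That is wider than 0.3365, so the effective and falls-short labels cannot both apply at this precision.

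**The case against.** A reader might infer that a technique missing p<0.05 is dropped. The article does not say so: significance identifies techniques, and the final choice also draws on interactions and constraints. The 30-40% is therefore the rate of failing the stated screen and not a rate of wrongful exclusion. This objection stands.

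The missing margin for calling a technique ineffective may sit in the full protocol, the SAP or the cited decision process, so its absence from an article is not in itself a fault. This also stands. The point rests on what is printed: the significance criterion, the unqualified guarantee and the statement about higher-order interactions.

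It can also be said that the shortfall is a sample-size problem. In part it is, because 28 per cluster is about half of what a main effect needs. But correcting the size alone would not justify the guarantee: at exactly 80% power one full-effect technique in five would still miss the screen.

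It is tempting to quote the chance of selecting exactly the right set of techniques, or a power for each interaction. The documents do not fix either. Set-selection rates depend heavily on whether effects add or multiply. With one PSU per condition, interaction power depends on contrast scaling and on an assumed between-PSU variance.

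Finally, selecting by significance is a legitimate choice, and interval labels leave more techniques undecided. That is a real cost, given under the fix.

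**Conclusion.** The point holds in limited form. The guarantee that the selected combination is the most effective and efficient is contradicted by the protocol's own inputs: a single technique with the full target effect misses significance about 30% of the time without loss and 39-40% with 20% loss, against the planned 20%. These figures assume a design effect of 2, standard errors valid at that value, a normal reference, and a technique acting alone on the 33.9% base. Across the other assumptions examined, the range runs from 5-11% to about 60%. The statement that the sample was increased to help detect higher-order interactions is likewise unsupported, since 640 does not reach 80% power even for a main effect. The documents do not show that non-significant techniques are excluded. The change should be made, and it is one of wording.

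**What to change.** In the decision paragraph of Data analysis:
- Judge each main-effect rate ratio and its 95% interval against the agreed ratio of 1.40. Report a technique as effective if the lower bound exceeds 1, as falling short of the target only if the upper bound is below 1.40, and otherwise as undetermined, to be decided on the estimate, cost and the predetermined constraints.
- State that a non-significant interaction will not be read as absence of antagonism.
- Replace the guarantee with a statement that the process aims to identify the best-supported combination.

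In Sample size and power:
- Restate main-effect power as about 60-70% at 640, with its assumptions.
- Delete the statement that the sample was increased for higher-order interactions, and do not replace it with nominal interaction powers.

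Cost: text changes before data are seen, with no extra clinicians or visits. At a design effect of 2 on the log scale, about 29-39% of full-effect techniques and 40-49% of null ones would be labelled undetermined, while only about 2.5% of full-effect techniques would be called short of the target. The rule needs standard errors that are valid with eight PSUs, whichever model supplies them.
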